**Exercise and rehabilitation [51,52]**			
	Personalized exercise programs	Develop individualized exercise programs that take into account the patient’s overall health status, VTE history, and comorbid conditions.	
	Supervised rehabilitation	Initially, provide supervised rehabilitation to ensure safe exercise practice and adjust the intensity and type of exercise as needed.	
	Long-term physical activity	Encourage long-term adherence to physical activity guidelines to improve health outcomes.	
**Management of vascular risks and comorbidities [53-57]**			
	Comprehensive vascular risk assessment	Conduct a thorough assessment to identify and manage modifiable vascular risk factors such as obesity, smoking, hypertension, and diabetes. Monitor for cardiac arrhythmias such as atrial fibrillation and obstructive sleep apnea.	
	Lifestyle modifications	Provide education and support for lifestyle changes, including dietary modifications, smoking cessation programs, and weight management strategies.	
	Integrated care for cardiovascular risks and comorbidities	Coordinate care among specialists to manage comorbidities effectively, ensuring that treatments for VTE are compatible with other medical conditions and medications.	

^a^DOACs: direct oral anticoagulants.

^b^INR: international normalized ratio.

^c^HAS-BLED: hypertension, abnormal renal or liver function, stroke, bleeding history or predisposition, labile INR, elderly (age ≥ 65 years), drugs or alcohol concomitantly.

^d^CTPA: computed tomography pulmonary angiography.

^e^VTE: venous thromboembolism.

^f^PTS: postthrombotic syndrome.

^g^PPES: postpulmonary embolism syndrome.

^h^CTEPH: chronic thromboembolic pulmonary hypertension.

^i^mHealth: mobile health.

#### The HBM and KAP-Combining Framework

The HBM suggests that people’s perceptions of the severity and susceptibility to a health issue, along with the perceived benefits and barriers to taking preventive action, influence their decisions to adopt health behaviors. The KAP highlights the sequential relationship among knowledge, attitudes, beliefs, practices, or behaviors. It posits that increased knowledge leads to changes in attitudes, which influence practices or behaviors. The key components of the HBM and the KAP are shown in Textbox 2. This study further extends the framework of the KAP by incorporating the HBM within the attitude domain. Through an in-depth analysis of the factors influencing the adoption of health behaviors, we believe that it will improve patients’ health beliefs, increase self-efficacy in health behaviors, and promote patient-centered management. Furthermore, this study has taken an additional step by incorporating the ABCDEF pathway for integrated management of VTE into the practice domain of the KAP, thereby assessing patient health behaviors more comprehensively. Figure 1 shows the combined HBM and KAP framework.

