#### Integrated VTE Management Pathway Within mVTEA

The long-term management of VTE is multifaceted, requiring individualized patient assessment and a nuanced approach to therapy. In this study, we have proposed the ABCDEF pathway for integrated management of VTE to complement mVTEA-assisted patient-centered management, thus minimizing the risk of VTE and its complications and ensuring patient safety and quality of life (QoL): (1) appropriate antithrombotic management; (2) bleeding risk management; (3) complication monitoring; (4) digital health management; (5) exercise and rehabilitation; and (6) facilitate the management of risk factors and comorbidities. Details of the integrated VTE management pathway are presented in Table 1.

**Table 1 table1:** The ABCDEF pathway for integrated management of venous thromboembolism.

Pathway and key point			Process

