**Digital health management [22-24,50]**			
	Telemedicine	Implement telemedicine platforms for regular follow-ups, reducing the need for in-person visits and enabling remote monitoring of anticoagulation therapy.	
	mHealth^i^ apps	Use mHealth apps that allow patients to track their medication adherence, report symptoms, and receive reminders for follow-up appointments.	
	Wearable devices	Encourage the use of wearable devices that monitor vital signs (eg, heart rate and oxygen saturation) to detect early signs of complications.	

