#### Routine VTE Management

The routine VTE management group will receive only conventional postdischarge management according to local clinical practice, including basic health advice appropriate for the prevention and treatment of VTE. The textual and graphical materials comprising the aforementioned basic package for VTE-related health education in the mVTEA app will be printed and distributed to patients within the routine management group on the day of discharge for home-based study. The video courses in the health education basic package can be accessed by scanning the QR code.

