### Outcome Measures

#### Primary Outcome

The primary outcome of this study is the difference in patients’ KAP on VTE at 3-month follow-up between the mVTEA management group and the routine management group.

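### The primary KAP total is likely to award some points for receiving the allocated app, because its practice domain incorporates a pathway with a digital-health element

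*Protocol article*

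**What the plan says.** The section on the combined HBM and KAP framework describes "incorporating the ABCDEF pathway for integrated management of VTE into the practice domain of the KAP", and gives the purpose as "thereby assessing patient health behaviors more comprehensively". The pathway therefore has a measurement role as well as a role in care. The section on mVTEA-facilitated management says that the VTE-KAP questionnaire was developed under the guidance of this joint framework.

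The section on the integrated pathway lists "4) digital health management" as one of six elements. Table 1 expands it into three key points: telemedicine ("Implement telemedicine platforms for regular follow-ups"), apps ("Use mHealth apps that allow patients to track their medication adherence, report symptoms, and receive reminders for follow-up appointments"), and wearable devices.

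The mVTEA app delivers education, medication reminders, adherence feedback, risk monitoring, access to health records and a channel to specialists. The comparison group "will receive only conventional postdischarge management according to local clinical practice", with printed materials and videos reached by QR code.

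The primary outcome is "the difference in patients’ KAP on VTE at 3-month follow-up between the mVTEA management group and the routine management group". The three domain scores are listed as secondary, which implies that the primary measure is the total. The only sensitivity analysis named under Statistical Analyses compares the ITT and FAS results.

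**The concern.** If practice questions award points for using an app, remote follow-up or a wearable, one arm is placed to collect them by allocation. A routine-care patient with equally good conventional self-management would need to find digital tools elsewhere to match. Part of the difference would then record that patients given an app use an app.

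The stated hypothesis is that the app improves knowledge, attitudes and practices compared with face-to-face visits. Points earned by receiving the app do not bear on it. The powered effect is only 5% of the score, so a few such items could make up much of it. Nothing in the article separates them: the secondary practice score contains the same items, and comparing two analysis populations cannot reveal the overlap.

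**Working it through.** **1. The link, step by step**

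| Step | Source | Status |
|---|---|---|
| Pathway incorporated into the practice domain, for assessment | HBM and KAP-Combining Framework | Stated |
| Questionnaire guided by that framework | mVTEA-Facilitated Patient-Centered VTE Management | Stated |
| Element D is telemedicine, apps, wearables | Integrated pathway section; Table 1 | Stated |
| Only one arm is given the mVTEA app | Intervention overview; Routine VTE Management | Stated |
| A scored item asks about digital use | Multimedia Appendix 1 | Not shown |

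The first four steps make the last one likely. They do not prove it.

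**2. Weight of the practice domain**

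- Questions: 26/53 = 49%.
- Points: 130/283 = 46% of the maximum, the largest domain.
- Knowledge and attitudes together: 53 + 100 = 153 of 283.
- Average maximum per practice question: 130/26 = 5 points.

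**3. The plan's own power figure**

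Inputs from Sample Size and Power Considerations: coefficient of variation 0.10, difference 5%, 100 per group, two-sided test.

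- d = 0.05/0.10 = 0.50. Noncentrality = d × √(n/2) = 0.50 × √50 = 3.536.
- Alpha 0.05: Φ(3.536 − 1.960) = Φ(1.576) = 94.2%. Stated: 94%.
- Alpha 0.025: Φ(3.536 − 2.241) = Φ(1.294) = 90.2%. Stated: 90%.

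Both figures reproduce. The sample-size statement is not at fault, and its inputs can be used below.

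**4. Illustration of what a few items could do**

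Three inputs are assumptions that the article does not give: a mean total of 190, the number of digital items, and a between-arm shift of 2 points per item. Six elements spread evenly over 26 questions would give 26/6 = 4.3 items each, so two to four items are used. It is also assumed that the intervention has no other effect on the score.

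- SD = 0.10 × 190 = 19. The 5% design effect = 9.5 points.
- Two items: 2 × 2 = 4 points. d = 4/19 = 0.211, noncentrality 0.211 × √50 = 1.489, Φ(1.489 − 1.960) = Φ(−0.471) = 32%.
- Four items: 4 × 2 = 8 points. d = 8/19 = 0.421, noncentrality 2.977, Φ(2.977 − 1.960) = Φ(1.017) = 84.5%. With the t distribution on 198 degrees of freedom it is 84.2%.

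**5. Sensitivity to the assumed mean**

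With the mean at 50% to 70% of the maximum (142 to 198) and SD at 10% of the mean:

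| Shift | Mean 142 | Mean 198 |
|---|---|---|
| 4 points | 51% | 30% |
| 8 points | 98% | 82% |

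Over the same means the 5% design effect is 7.1 to 9.9 points, so 8 points is about the whole of it.

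**The case against.** The strongest reply is that the questionnaire cannot be seen. The passage on incorporation concerns the practice domain of the KAP framework and does not name the questionnaire; the connection runs through the later statement that the framework guided its development. Table 1 is worded largely as provider actions, so how element D maps to patient questions is unknown. All of this stands. A reader might infer that the score is known to count the intervention itself, and the article does not support that.

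A reader might also infer that a positive result would be wholly circular. That is not supported either. Element D is one of six, practice is one of three domains, and 153 of the 283 points lie outside it. No text says that wearables are supplied to either arm. Control patients must also be able to use smart devices, they answer web-based questionnaires, and nothing stops them from using other apps. It cannot be said that they would necessarily score low.

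The percentages are correct arithmetic on assumed inputs. The per-item scoring is itself uncertain: 26 questions all scored 1 to 5 would range from 26 to 130, whereas the article gives 21 to 130.

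Finally, the secondary domain scores would show whether a gain was confined to practice. That helps, but it does not isolate digital items within practice. Redefining the primary total after 185 enrolments is also hard to defend for a scale developed by Delphi rounds with reported reliability. That argues for a supportive analysis, not for leaving the matter alone.

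**Conclusion.** The concern holds as a likely overlap between outcome and intervention. The article states that the scored practice domain incorporates a pathway with a digital-health element, that one arm is given an app of that kind, and it provides nothing to remove or separate the points concerned. It does not establish that any particular item scores app use, nor how many do.

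The size is therefore unknown. Under the assumptions above (mean 190, SD 19, two to four items shifted by 2 points each, no other effect, 100 per arm), the chance of a significant primary result from these items alone is about 32% to 84%. Those figures show that the point could matter against a 5% design effect; they do not estimate bias in this trial. If Multimedia Appendix 1 contains no items on digital use, the point closes.

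**What to change.** Before database lock, and blind to allocation, go through the practice questions and list any that score use of apps, telemedicine or wearables. If there are none, one sentence saying so is enough.

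If there are some:

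- Keep the full KAP total as the primary outcome.
- Prespecify the KAP total and the practice score without those items as a key supportive analysis, using the same model.
- Report the listed items separately, as a measure of uptake.
- State in advance that the claim of improved KAP will be limited if the difference does not persist without them.

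This needs no new data. The cost is one extra analysis on a slightly shorter scale, for which the reported reliability coefficients would not carry over. The observed difference on that scale may well be smaller.

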**Figure 1 figure1:**
[figure not shown]
Combined framework based on the health belief model and the knowledge, attitude, and practice approach. HBM: health belief model; VTE: venous thromboembolism.

The key components of the health belief model and the knowledge-attitude-practice frameworks.
**Health belief model**
Perceived susceptibility: belief about the likelihood of getting a disease or condition.Perceived severity: belief about the seriousness of the disease or condition.Perceived benefits: belief in the effectiveness of taking action to reduce the risk or severity.Perceived barriers: beliefs about the obstacles to taking the recommended action.Cues to action: triggers that prompt individuals to take action, such as symptoms or media campaigns.Self-efficacy: confidence in one’s ability to take the recommended action.
**Knowledge-attitude-practice**
Knowledge: awareness or understanding of health-related information and facts.Attitude: beliefs, feelings, and values toward a particular health issue or behavior.Practice: the actual behaviors or actions taken in response to health knowledge and attitudes.

#### mVTEA-Facilitated Patient-Centered VTE Management

To achieve the goal of mVTEA-facilitated patient-centered VTE management, an mVTEA-assisted patient health education program has been structured around the joint HBM and KAP framework as shown in Figure 2. To begin with, in a pilot study, we have developed a structured VTE-KAP questionnaire (Multimedia Appendix 1), guided by this joint theory framework, via 2 rounds of Delphi surveys among the National VTE Prevention and Treatment Program Office Expert Group and the VTE Prevention and Treatment Nursing Expert Group of the Chinese People’s Liberation Army General Hospital. This questionnaire demonstrated an overall Cronbach α coefficient of 0.959, with domain-specific coefficients of 0.885 for knowledge, 0.942 for attitudes, and 0.970 for practices. In addition, the overall split-half reliability coefficient was 0.834, with domain-specific coefficients of 0.879 for knowledge, 0.770 for attitudes, and 0.863 for practices.

**Figure 2 figure2:**
[figure not shown]
Specific intervention process of the mHealth app for patient-centered venous thromboembolism management. KAP: knowledge, attitude, and practice; mVTEA: smart technique-assisted patient-centered care mHealth app for managing venous thromboembolism; VTE: venous thromboembolism.

The VTE-KAP questionnaire is a self-administered questionnaire that includes demographic characteristics and KAP of patients toward VTE prevention and treatment. It is intended to evaluate the efficacy of health education programs and to inform the deployment of mVTEA-based health education strategies. This questionnaire consists of a total of 53 questions with an overall score range of 41-283. The knowledge domain contains seven questions to assess patients’ levels of knowledge regarding VTE prevention and treatment. The total score of knowledge for each study participant ranged from 7 to 53. The attitude domain contains 20 questions to assess patients’ attitudes toward VTE prevention and treatment. Each question was scored, and the ﬁnal attitude score ranged between 20 and 100. The practice domain contained 26 questions with a score range of 21-130 for assessing the implementation of VTE prevention and treatment behaviors in the study patients. The higher the score, the higher the level of knowledge, attitude, and practice.

To grade the KAP about VTE prophylaxis and treatment, the VTE-KAP questionnaire score is calculated according to the score ratio: score ratio=item score/total score of the item×100%. According to the previous study [58], a score ratio of ≥50% in the knowledge domain is classified as satisfactory and <50% as unsatisfactory; a score ratio of ≥60% in the attitude domain is classified as positive attitudes and <60% as negative attitudes; and a score ratio of ≥60% in the practice domain is classified as a good level of practice and <60% is classified as poor practice.

These VTE-KAP assessment outcomes determine the subsequent interventions delivered via the mVTEA app. Initially, upon registration, the mVTEA app delivers a standardized VTE education package containing 3 videos and 4 graphic resources covering VTE fundamentals, risk factors, symptoms, and prevention and treatment strategies. Following this initial phase, interventions are personalized based on the individual’s VTE-KAP scores. Tailored components include specific education schedules (basic or intensive), medication reminders, adherence feedback, risk monitoring features, access to electronic health records, and specialist communication channels. In addition, the mVTEA patient terminal automatically dispatches all health education questionnaires and home-rehabilitation reports according to the schedule specified in Table 2. The detailed workflow of this mVTEA-facilitated patient-centered VTE management strategy is presented in Figure 2, and the core functional interface of the mVTEA app is shown in Figure 3.

**Table 2 table2:** Distribution schedule of home rehabilitation reports and health education questionnaires for mHealth app-assisted, patient-centered venous thromboembolism management.

Timepoint	At discharge	1st month	2nd month	3rd month	6th month	9th month	12th month	>1 year
Home rehabilitation reports	None	✓	✓	✓	Once a month	Once a month	Once a month	Once a month
Knowledge questionnaire	✓	None	None	✓	✓	None	✓	Once every 6 months
Attitude questionnaire	✓	✓	✓	✓	✓	✓	✓	Once every 6 months
Practice questionnaire	✓	None	None	✓	✓	None	✓	Once every 6 months

**Figure 3 figure3:**
[figure not shown]
Core functional interface of the mHealth app for patient-centered venous thromboembolism management. (A) Health education program, (B) thrombosis risk assessment, (C) bleeding risk assessment, (D) anticoagulation management, and (E) home rehabilitation report.

#### Routine VTE Management

The routine VTE management group will receive only conventional postdischarge management according to local clinical practice, including basic health advice appropriate for the prevention and treatment of VTE. The textual and graphical materials comprising the aforementioned basic package for VTE-related health education in the mVTEA app will be printed and distributed to patients within the routine management group on the day of discharge for home-based study. The video courses in the health education basic package can be accessed by scanning the QR code.

### Outcome Measures

#### Primary Outcome

The primary outcome of this study is the difference in patients’ KAP on VTE at 3-month follow-up between the mVTEA management group and the routine management group.

#### Secondary Outcomes

Secondary outcomes include scores on each domain of the VTE-KAP questionnaire (knowledge domain, attitude domain, practice domain), QoL, VTE events, chronic thromboembolic pulmonary hypertension, chronic thromboembolic pulmonary disease, post-PE syndrome [13,48], International Society on Thrombosis and Hemostasis (ISTH) defined major bleeding events [59], VTE-related hospitalizations, VTE-related rehospitalizations, all-cause deaths, PE-related deaths, and new-onset of atrial fibrillation (AFI) or atrial flutter (AFL) at 3-month follow-up. For patients with more than 1 event, only the first event will be counted. A total of 3 investigators who are unaware of patients’ group assignments will adjudicate all endpoints.

Generic, nondisease-speciﬁc health-related QoL is assessed using the EQ-5D-5L questionnaire and its corresponding visual analog scale [60]. Brieﬂy, the EQ-5D-5L generates an overall index that ranges from 0 (lowest generic QoL) to 1 (highest generic QoL) and is calculated based on country-speciﬁc reference value sets. The EQ-5D-5L health index was calculated with the value set for China. The EuroQol visual analog scale ranges from 0 to 100, with higher scores indicating better health.

VTE events are categorized into 3 groups: new-onset VTE, hospital-acquired VTE (HA-VTE), and recurrent VTE. VTE that occurred for the first time during the study period is classified as new-onset VTE. HA-VTE is defined as any new-onset VTE that has occurred within 90 days of hospital discharge [4]. Recurrent VTE is defined as the appearance of new evidence of VTE after acute VTE has been treated in the acute phase (2 weeks) with significant clinical improvement in signs and symptoms. According to the time of VTE recurrence, it is further categorized into early VTE recurrence (within 3 months after the last VTE occurrence) and late VTE recurrence (more than 3 months after the last VTE occurrence) [61]. Hospitalization due to the new-onset VTE will be documented as VTE-related hospitalizations, while rehospitalization due to VTE recurrence, progression, or complications arising from VTE treatment will be classified as VTE-related rehospitalizations. All-cause death refers to any death occurring during the study period, regardless of the cause. PE-related death is defined as death explicitly caused by PE.

New-onset AFI or AFL is defined as an episode of AFI or AFL lasting at least 30 seconds, first detected by devices such as smart wearable devices or ambulatory electrocardiograms, or initially diagnosed during a medical visit and documented in outpatient charts or inpatient hospital records.

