**Complication monitoring [13,44,48,49]**			
	Regular complication surveillance	Schedule regular check-ups and use diagnostic imaging (eg, Doppler ultrasound, CTPA^d^) to monitor for complications such as recurrent VTE^e^, PTS^f^, PPES^g^, or CTEPH^h^.	
	Patient self-monitoring	Encourage patients to report new or worsening symptoms promptly, and provide them with clear instructions on what to look out for.	

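### Hazard ratios for AF/AFL, and possibly for VTE and post-PE complications, can reflect unequal detection because surveillance is described only for the app arm

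*Protocol article*

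**What the plan says.** **Definitions.** Under Secondary Outcomes, AF/AFL qualifies at 30 seconds or more, either when "first detected by devices such as smart wearable devices or ambulatory electrocardiograms" or when first diagnosed and documented at a medical visit. New-onset VTE is any first VTE in the study period, and recurrent VTE is new evidence of VTE after a treated acute episode. Neither requires symptoms at the new event.

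**App arm.** The section Integrated VTE Management Pathway Within mVTEA states: "we have proposed the ABCDEF pathway for integrated management of VTE to complement mVTEA-assisted patient-centered management". Table 1 then lists, among its processes:
- Digital health management: "Encourage the use of wearable devices that monitor vital signs (eg, heart rate and oxygen saturation) to detect early signs of complications".
- Management of vascular risks and comorbidities: "Monitor for cardiac arrhythmias such as atrial fibrillation and obstructive sleep apnea".
- Complication monitoring: "Schedule regular check-ups and use diagnostic imaging", with recurrent VTE, PPES and CTEPH among the targets, and "Encourage patients to report new or worsening symptoms promptly".

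**Control arm.** Under Routine VTE Management, controls "will receive only conventional postdischarge management according to local clinical practice", with basic advice and printed or QR-code education.

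**Ascertainment and analysis.** Table 3 collects events once, at month 3. Follow-up is by visit, telephone or, in the app arm, the platform. Three investigators unaware of allocation adjudicate all endpoints. Statistical Analyses compares events by Cox model, accounting for the prestratification factors. It omits a safety analysis set on the ground that the outcomes already cover safety.

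**The concern.** A between-arm hazard ratio measures a difference in incidence only if an event has the same chance of being found in each arm. Here some of the searching belongs to the intervention, and the endpoint definitions accept what that searching finds. AF/AFL is the clearest case: a short episode recorded by a wearable is an event, and wearables are promoted in one arm only.

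The stated safeguards act elsewhere. Blinded adjudication classifies events that have come to light; it cannot recover an episode never recorded in a control. Adjustment for age group and VTE status does not touch the problem either.

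The event outcomes also carry the safety half of the hypothesis, since no separate safety set is planned. An excess of detected AF/AFL could be read as harm, or could hide a real benefit.

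**Working it through.** **1. The plan's own figures.** No event rate, detection rate or power is stated for the clinical outcomes. The sample size concerns the KAP score. With a CV of 0.1, a 5% difference and 100 per group, 0.05 / (0.1 × √(2/100)) = 3.54, and Φ(3.54 − 1.96) = 94%, as stated. This point does not depend on that calculation.

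**2. The arms side by side.**

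| Route of detection | App arm | Routine arm |
|---|---|---|
| Wearables | Encouraged (Table 1) | Not described |
| Arrhythmia monitoring | Listed (Table 1) | Not described |
| Check-ups with imaging | Listed, no dates (Table 1) | Not described |
| Prompt symptom reporting | Encouraged (Table 1) | Not described beyond basic advice |
| Month-3 event collection | Yes (Table 3) | Yes (Table 3) |

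**3. Illustration with no true effect.** Let r be the true 3-month risk, equal in both arms, and let sC and sE be the probabilities that an event is detected in the control and app arms. All three are assumptions. Then

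apparent HR = ln(1 − r·sE) / ln(1 − r·sC), which is close to sE/sC when r is small.

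Expected detected events = 128 × r × (sC + sE). The approximate chance of a significant excess in the app arm is Φ(√events × ln HR / 2 − 1.96).

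For r = 5%, sC = 0.50 and sE = 0.75: ln(0.9625) / ln(0.975) = 1.51, with 128 × 0.05 × 1.25 = 8.0 events.

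| sC | sE | Apparent HR at r = 5% | Range, r = 2% to 10% | Events at r = 5% | Chance of significance at r = 5% | True HR that would appear as 1 (sC/sE) |
|---|---|---|---|---|---|---|
| 0.50 | 0.50 | 1.00 | 1.00 | 6.4 | – | 1.00 |
| 0.50 | 0.60 | 1.20 | 1.20–1.21 | 7.0 | 4% | 0.83 |
| 0.50 | 0.75 | 1.51 | 1.50–1.52 | 8.0 | 8% | 0.67 |
| 0.50 | 0.90 | 1.82 | 1.81–1.84 | 9.0 | 14% | 0.56 |
| 0.30 | 0.90 | 3.05 | 3.02–3.10 | 7.7 | 34% | 0.33 |

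Over r = 2% to 10% and the unequal-detection rows, expected events run from about 3 to 18 and the chance of significance from about 4% to 60%. These show the mechanism; they do not estimate this trial's bias. If detection were lower in the app arm, the ratios would fall below 1.

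**4. Does restricting to symptom-prompted events cure it?** Suppose surveillance in the app arm finds, early, a share d of events that would later have become symptomatic. Excluding them leaves (1 − d)·r in the app arm against r in controls. With no true effect the restricted HR is about 1 − d: 0.70 for d = 0.3 and 0.50 for d = 0.5. The restricted analysis can therefore err in the app's favour, while the all-events analysis can err against it.

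**The case against.** A reader might infer that controls receive no surveillance, that all the planned hazard ratios are biased, and that the app arm must show more AF, VTE and post-PE complications. The document does not support that much, for these reasons:

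- **Routine care is undescribed, not shown to lack testing.** Local practice may include imaging or rhythm checks, and hospital-wide VTE training reaches all staff. A condensed article need not list them. This stands as a limit on the claim, but nothing in the document requires similar searching in both arms.
- **App-arm surveillance is stated as principle.** Table 1 encourages and gives examples. No wearable is supplied, and Tables 2 and 3 set no imaging or rhythm-monitoring timepoint. Patients unable to use smart devices are excluded from both arms, so controls may own wearables too. This weakens any claim about size.
- **Direction is not fixed.** The same Table 1 section uses telemedicine to cut face-to-face attendance, and the comparator is described as traditional face-to-face care. Fewer examinations could lower detection of VTE and post-PE outcomes in the app arm. This stands. Excess AF/AFL remains the most plausible result because the wearable route is named in both the definition and the pathway.
- **Scope is limited.** No differential search is shown for deaths or major bleeding, and the KAP outcome does not depend on event detection.
- **The article already calls for caution.** Its Limitations section says the clinical outcomes need later validation, and few events are likely. That tempers the consequence, but the section does not mention unequal detection.

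Symptom-prompted events are not a clean alternative as the sole comparison either: the pathway also prompts symptom reporting, and step 4 of the working shows the bias can reverse.

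**Conclusion.** The point holds in limited form. The AF/AFL definition and the app-arm pathway together allow unequal ascertainment, and neither blinded adjudication nor covariate adjustment removes it. It bears chiefly on AF/AFL and possibly on VTE and CTEPH/CTEPD/PPES. The likely direction for AF/AFL is an excess in the app arm; for the others it is open.

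The size is unknown. The apparent hazard ratios of about 1.2 to 3.1 rest wholly on assumed detection probabilities, an assumed risk of 2% to 10% and no true effect. Deaths, major bleeding and the primary outcome are not materially affected. It is worth correcting because these outcomes are the trial's stated safety assessment, and the data needed to interpret them are cheap to record.

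**What to change.** 1. For each AF/AFL, VTE, CTEPH, CTEPD and PPES event, record from source records how it was first detected: symptoms or unscheduled care, scheduled surveillance, or wearable. Someone other than the blinded adjudicators should complete this field, because the route could reveal allocation.
2. Tabulate these events by detection route and arm.
3. Keep the all-events Cox analysis. Add a sensitivity analysis, pre-specified before database lock, that excludes wearable-only AF/AFL and surveillance-only VTE/CTEPH/CTEPD/PPES.
4. State that the two analyses can be biased in opposite directions, and draw no safety or harm conclusion on these outcomes unless they agree.

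No change to patient care is involved. The cost is some extra abstraction, including retrospectively for patients already enrolled (185 of 256, or 72%, at submission), and sparser events in the sensitivity analysis.
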